#### Incentives and counseling arm

Finally, those couples in the incentive and counseling arm will participate in all activities described for the incentives arm and also decide on a day of the week and time to come for BCT counseling. There will be a total of four sessions covering topics related to alcohol use, relationships, and communication. Each session will last for approximately 1 h. Sessions will be conducted by lay counselors who will be trained on BCT facilitation. Additionally, a clinical psychologist trained in CBT (ST) will supervise counselors and observe a subset of counseling sessions to monitor fidelity and measure quality of implementation.

While BCT is generally conducted over a significant duration of time rather than constrained to a discrete number of sessions, our pilot was designed to test the feasibility and resonance of key concepts and activities. The first BCT session will include an introduction to a “daily trust contract” during which the male partner verbally commits to reduce his drinking and his female partner acknowledges her support. The first session will also include a relaxation exercise to aid in overcoming the urge to drink. During the second session, the daily trust contract will be revisited and an activity to identify and avoid triggers to alcohol use on the way home will be introduced. Other strategies to avoid drinking will also be discussed, including the relaxation exercise, reviewing positive reasons for sobriety, distracting activities, and positive self-talk. The third session will include a review of prior alcohol avoidance strategies, as well as an activity aimed at encouraging caring behaviors between partners. In the final session, couples will review the caring behavior activity and will be introduced to the concept of active listening. All sessions will include role plays and end with assignments that couples will be asked to practice between sessions.

### Staff training and quality assurance

Prior to initiating this study, the local research team, composed of a study coordinator, interviewers and outreach workers, will attend a series of two training sessions. The first will consist of a 5-day research protocol training to familiarize the team with the study aims, protocol, and all research procedures. Research and intervention staff will be separated in their roles, however both will be familiarized with the overall study aims and procedures. Interviewer training will stress the importance of building rapport, active listening, asking questions with sensitivity and maintaining confidentiality of participants' responses. Study teams will receive information and training on reporting of social harms and how to assist or refer participants for emotional and social support, should any participant experience distress during an interview. Given the inclusion of alcohol use and IPV in these interviews and the selection of women who may likely have experienced violence, particular care will be taken to develop a close referral network of organizations providing alcohol de-addiction and IPV services through which participants can be referred. Additionally, all members of the research team will undergo research ethics training, which includes close attention to confidentiality and the protection of research participants. All trained staff, including members of our community partner, will be asked to take an oath indicating their commitment to protecting participant confidentiality.

The second training session for the study staff will be held just prior to the intervention component of the study and will consist of a 5-day training to again review the study aims, as well as train study staff in-depth on all intervention procedures, including the counseling.

### Data collection and management

Unique identification codes will be assigned to each data collection event and each study participant. These codes will be used to identify associated surveys, transcripts, breathalyzer data, as well as any individual-level information collected in data collection tracking forms. No names or other identifiable personal data will be collected in addition to the audio recordings or survey data and none will be associated with responses.

#### Breathalyzer data management

Data (time of test, photo, unique identification code, and BAC reading) will be directly transmitted to the SoberLink© system (web portal and secure server) which can be accessed only by selected team members. The SoberLink© system is US FDA approved. At the end of each week, a CSV file containing de-identified data including unique identification code, timestamp, and BAC score will be sent to the study team via email. Data will be reviewed for completeness and merged with survey data using the unique identification code.

#### Survey data management

Individual survey data collection will be done using tablets and sent electronically to a database for review on a regular basis. The use of electronic data collection on tablets will allow the data to be reviewed as it is collected. Each data collector will carry paper copies of the survey in case they confront problems with the tablet. If a survey must be completed on the paper form, the interviewer will reenter the data into his/her tablet immediately after returning from the field and resolving the issue with the tablet. To ensure confidentiality, the device will be password protected.

All local staff will be trained in maintaining participant confidentiality and rigorous data management based on standard operating procedures. All electronic files will be reviewed for completeness and accuracy.

#### Qualitative data management

All in-depth interview (IDI) guides will be translated to the local language (e.g., Kannada) and confirmed by a second qualified translator to ensure accuracy prior to conducting the interviews. IDIs will be recorded to ensure an audit of the content and process is possible. Permission for recording will be documented on the consent form. Only those who provide such permission will be included in the qualitative arm of the study.

IDI recordings will also be transcribed and translated into English (when needed) and typed into word processing files. These files will be uploaded into NVivo (or a similar qualitative software program) and thematically coded using a structured codebook, by trained analysts.

### Sample size

The sample size is anticipated to be 60 couples (20 per intervention arm). While this sample size is not powered to detect significance, it is similar to that used in our prior research of pilot interventions and is in line with recommendations that studies of this kind have a sample size of 24–50 (33–35). We anticipate attrition of approximately 20%, so our goal is to enroll 10–12 more couples to buffer these losses, yielding a final sample size of around 60 couples.

### Analysis

#### To evaluate the feasibility of implementing beautiful home

To evaluate implementation feasibility, we will calculate recruitment and retention rates and evaluate whether we had differential retention by study arm. We will stratify these assessments by arm to determine whether implementation feasibility differed, and will also measure contamination. If possible, we will also stratify assessments by level of alcohol use based on participants' breathalyzer scores. This will help us to determine whether participants with higher or lower alcohol use were more likely to complete the intervention.

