**Figure 1 F1:**
[figure not shown]
*Beautiful Home* intervention Theory of Change (TOC).

The study will be conducted with 60 couples randomized into one of three arms: an incentive-only arm, an incentive-plus-counseling arm, and a comparison arm. The design mimics the proposed design of a follow-on randomized control trial, and allows for testing the feasibility and acceptability of the study design, as well as offering an opportunity to determine whether the combined approach of incentives and counseling performs better than an incentive-only intervention. During the intervention, breathalyzer data will be collected daily for the first 4 weeks from men using Soberlink© breathalyzer technology that allows for photo capture to ensure the appropriate person is taking the test. A period of 4 weeks was chosen for the incentives portion of the intervention based on the duration of Schilbach's study (10) and to preserve the team's flexibility to adapt if the initial incentive structure was not affecting drinking. Participants in the incentive-plus-counseling arm will participate for an additional 2 weeks (6 weeks) to accommodate counseling sessions. No breathalyzer data will be collected for the additional 2 weeks. Women and men will complete a baseline survey, as well as surveys immediately and 3 months post-intervention. A sub-sample of male and female participants from each study arm (~4 couples per arm) will participate in qualitative in-depth interviews to gain feedback about their participation in the intervention, including around processes of change (i.e., what pathways contribute to changes in alcohol and violence reduction) that might inform the content of future interventions. See Figure 2 for a diagram of study flow and data collection points.

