### Randomization

Participants will be randomized at the couple-level prior to the start of the intervention by a statistician using a random number generator. Their randomization assignment will be revealed during an orientation session using a sealed envelope with their study ID.

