### Study population

Our screening procedures will be designed to identify couples who would benefit from the study (i.e., those with problems related to alcohol and IPV), as well as to minimize the potential risk experienced by participants. The protocol achieves this by screening out men with severe alcohol dependence and experience of severe violence among women. The screening tool for men will utilize the AUDIT-C (23) to screen out non-drinkers and the Severity of Alcohol Dependence Questionnaire (SADQ) to screen out men with severe alcohol dependence syndrome. The SADQ was chosen based on its prior use by the World Health Organization (WHO) in multiple low-income countries, and its reliability and validity (24). During the screening process, men who score 31 or higher on SADQ and are deemed to be severely dependent will not be included in the study. Men who score as moderately dependent (16-30 on the scale) will be initially waitlisted until the team can determine the safety of enrolling these participants considering the possibility that these individuals may develop severe or complicated alcohol withdrawal syndrome requiring medical intervention. This subset of men will undergo a second medical screening by the study physician using the Clinical Institute Withdrawal Assessment for Alcohol Scale (CIWA-AR) (25) and those scoring above 8 on this scale will be excluded from the study.

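### The breathalyzer scores proposed for stratifying completion are recorded after randomisation and are the target of the incentives, so they cannot show which drinkers are retained; the screening AUDIT-C score can

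*Protocol article*

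**What the plan says.** In the protocol article, Analysis, under the heading on evaluating the feasibility of implementing Beautiful Home, recruitment and retention are to be assessed by arm. The next step, introduced with the words if possible, is: "we will also stratify assessments by level of alcohol use based on" the men's breathalyzer scores. Its stated purpose is to "determine whether participants with higher or lower alcohol use were more likely to complete the intervention".

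The timing of those scores is given elsewhere. Under Randomization: "Participants will be randomized at the couple-level prior to the start of the intervention". Under Study design, in the text after Figure 1: "During the intervention, breathalyzer data will be collected daily for the first 4 weeks from men using" the Soberlink device, and for the longer counseling arm, "No breathalyzer data will be collected for the additional 2 weeks". Under Study activities by arm, the orientation session covers how to use the device and a baseline survey; no baseline breath reading is described.

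Alcohol measures from before randomisation do exist. Under Study population: "The screening tool for men will utilize the AUDIT-C (23) to screen out non-drinkers". The SADQ is also part of the men's screening. The analysis paragraph uses neither as a stratifier.

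**The concern.** The question is which kind of drinker stays in the study. A variable that answers it should be fixed before the arms can act, be measured the same way in every arm, and be available for men who leave. The breathalyzer score falls short on each count.

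- **The arm acts on it.** Men in the incentive arms are paid more for negative tests, and male sobriety is one of the outcomes listed under Objectives. A heavy drinker who responds moves into the lower stratum.
- **It may not track level of use under incentives.** The Introduction reports that in the earlier incentive trial among rickshaw drivers, drinking fell around test times but rose at other times, with no overall reduction.
- **It is measured differently by arm**, in number of tests and in time of day.
- **Its completeness depends on the outcome.** A man who leaves in the first days has little or nothing to classify him by.

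Retention is the first feasibility objective, and the pilot is meant to inform the design of a larger trial. A distorted answer about which drinkers complete would be an unhelpful thing to pass on.

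**Working it through.** **The plan's own figures.** No stated figure rests on this analysis. The nearest are under Sample size: 3 × 20 = 60 couples, and 48/(1 − 0.20) = 60, a buffer of 12 (the base of 48 is inferred). They reproduce and do not bear on the point.

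**Order of events.** Screening with AUDIT-C and SADQ; randomisation; orientation, where the assignment is revealed and the baseline survey completed; breath tests in weeks 1 to 4; counseling-arm activity to week 6; 3-month survey. Every breath score described falls after randomisation.

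**Prompted tests in 28 days.**
- Comparison arm: every other evening, 28/2 = 14; at the abstract's three a week, 3 × 4 = 12.
- Incentive arms: twice daily, 2 × 28 = 56; if daily, 28.

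**Illustration of size.** None of these inputs is in the documents. Baseline drinking is standard normal and half the men are heavy (above 0). On-study score = baseline − shift × (incentive arm) + error with SD 0.5; a score above 0 is high. Two thirds of couples are in an incentive arm. Dropout time is uniform over 28 days, and 7 days of readings are needed to classify a man, so 7/28 = 25% of dropouts are unclassified. There are 600,000 simulated couples.

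(a) *True completion 70% in heavy and 90% in light drinkers, a gap of −20 points.*
- Effect of missing scores alone. Classified share: heavy 0.70 + 0.30 × 0.75 = 0.925; light 0.90 + 0.10 × 0.75 = 0.975. Completion among those classified: 0.70/0.925 = 75.7% and 0.90/0.975 = 92.3%, a gap of −16.6.
- Adding random error, which misplaces 15% of men. High stratum: (0.85 × 0.70 + 0.15 × 0.90)/(0.85 × 0.925 + 0.15 × 0.975) = 0.730/0.9325 = 78.3%. Low stratum: 0.870/0.9675 = 89.9%. The gap is −11.6 (simulated −11.7).
- Adding the arm effect:

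| Shift (SD) | Heavy incentive men classed low | Heavy comparison men classed low | Gap shown |
|---|---|---|---|
| 0 | 15% | 15% | −11.7 |
| 0.5 | 38% | 15% | −11.3 |
| 1.0 | 63% | 15% | −9.7 |
| 1.5 | 82% | 15% | −8.4 |

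Missing scores cost 20.0 − 16.6 = 3.4 points and the arm effect up to 11.7 − 8.4 = 3.3. The step between, 16.6 − 11.6 = 5.0, is ordinary error. The comparison measure here is error-free; a real AUDIT-C score would carry some error too.

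(b) *Completion unrelated to baseline drinking, but 15 points different between arms.* With comparison 90% and incentive 75%, the gap shown is +2.3, +4.1 and +6.5 points at shifts of 0.5, 1.0 and 1.5 SD. With comparison 70% and incentive 85%, it is −2.1, −4.0 and −6.4. The true gap is 0, and the sign follows whichever arm loses more.

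**The case against.** The case for leaving the plan alone has substance.

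- **It is conditional and descriptive**, in a pilot stated not to be powered. This stands and limits the consequence, but if possible speaks to whether the analysis can be done, not to what it would mean.
- **The sentence does not say baseline use.** Whether men who are still drinking on study stop taking part is a legitimate question. This stands, and is a reason to keep breath scores as a within-arm description. It is a different question from which drinkers are retained.
- **The paragraph already stratifies by arm.** Reading within arm removes the artefact between arms. It does not remove response within an arm, or missing scores. The planned comparison of people with and without missing data is partial cover only, since it does not name alcohol use.
- **The distortion is small against the sample.** One couple is 1/20 = 5 points of an arm, so the shifts above amount to one or two couples. This stands.

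Three stronger readings are tempting and not supported. A reader might infer that 0.20 × 60 = 12 couples would lack scores; the stated attrition has no time attached, and couples lost after week 4 can have every reading. A reader might infer that eligibility for the follow-on trial would be misled; the criteria under Expected outcomes and results do not include completion by drinking level, and the alcohol exclusions are set on safety grounds. A reader might infer that heavier drinkers would look harder to retain than they are; case (a) shows a real gap shrinking, and in case (b) the sign can go either way.

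**Conclusion.** The concern holds in a limited form. As described, the breathalyzer score is recorded after randomisation, is acted on by the arm, is collected on different schedules, and is few or absent for early leavers. Strata built on it blend prior drinking, response to the arm and time on study, so they cannot show whether heavier or lighter drinkers complete more often.

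This conclusion rests on the order of events in the article and on no baseline breath reading being described; the analysis paragraph does not itself say when its scores are taken. The sizes in the illustration rest on assumed inputs and show only that the distortion can be several points in either direction. This is a worthwhile correction to a secondary feasibility analysis, not a threat to the trial's main conclusions.

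**What to change.** Change the sentence in the feasibility analysis so that retention and completion are summarised, pooled and by arm, by a measure taken before randomisation.

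- **Preferred:** the screening AUDIT-C score, with the cut-point fixed without sight of completion.
- **Secondary option:** SADQ below 16 versus 16 to 30. State its limits: men at 31 or above are excluded, and those at 16 to 30 are waitlisted and pass a second screen, so the upper band is truncated, selected and may be small, especially by arm.
- **Less suitable:** alcohol use from the baseline survey, because it is completed at the session where assignment is revealed.

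Keep breathalyzer results as an outcome and as a measure of adherence to testing. If they are set against completion, do so within arm only, label them as on-study drinking, and report how many men have too few readings to classify.

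The cost is a reworded sentence or two. No new data are needed, since the men's screening already includes both scores.

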#### To assess effects on safety and intermediate outcomes

Descriptive statistics will be calculated to describe participants' social and economic characteristics, relationship factors, gender norms and attitudes, and alcohol use risk behaviors. Descriptive statistics will also be calculated separately by intervention arm so that variations in distributions can be examined.

Most measures to be used in the analyses have been reported and validated in earlier studies. For some (e.g., gender norms), items will be grouped into scales conceptually and by examining item correlations through the use of factor analysis and other multidimensional scaling techniques.

We will examine whether there are systematic differences between individuals with missing data and those without. If missing data appear to be informative (e.g., missing systematically), we will employ appropriate ad hoc imputation methods to impute missing values.

#### Qualitative data analysis

In-depth interview data will be analyzed for dominant themes using grounded theory techniques. We will use textual data coding as a primary qualitative analytical approach to summarize, extract meaning, and condense the data, using NVivo qualitative software. Transcripts will be coded first through descriptive coding for key themes and topics, using a preliminary codebook. Additional codes will be identified through an iterative process of reading the textual data to identify emergent themes, and the codebook will be modified accordingly. Pattern codes, which achieve a greater level of abstraction, will be used to start linking themes and topics together to explore the relationship between various constructs described in the socio-ecological framework. (36) The findings and interpretations of the data will be critically discussed by the investigators until group consensus is reached on the dominant themes and meanings. Key findings will also be used to inform the refinement of the intervention and accompanying research materials for evaluation in a future randomized control trial.

#### Expected outcomes and results

This pilot study will provide information to determine the design of a future effectiveness trial. Specific outcomes include ability to recruit participants and retain couples across the three arms of the study. We will also assess the effects of intervention on household safety and male partner sobriety, and attitudes and behavior related to gender equality and shared household decision making. Results pertaining to outcomes will be available after the 3 month follow-up following the intervention. The study results will be presented at National and International Research meetings and published in peer reviewed scientific journals. Findings from this pilot study in favor of a follow-on trial will include the following: (1) the intervention is safe and feasible (i.e., no harmful events directly related to the intervention are detected); we are able to recruit participants in a timely manner; loss to follow-up is less than 20% overall and similar in all study arms; and no contamination is detected or if detected, appropriate design changes can be instituted; (2) data on outcomes support the impact of the intervention on alcohol use reduction and couples' communication skills; and trends in alcohol use and IPV incidence are in the direction that supports the positive impact of the intervention; and (3) qualitative evidence similarly supports the feasibility, safety and beneficial impact of the intervention. In conclusion, this study will generate important insights on a novel, urgently needed response to IPV in a high prevalence setting.

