While Standard WHO questions (26) on violence have been reliably used to measure violence in low and middle-income countries, no studies were identified that clearly documented procedures for screening out women experiencing severe violence whose risk may be increased by a couples-level violence prevention intervention. Following a risk averse model, the study team initially defined severe violence as the following types of violence occurring in the past two years: (a) being hit with a fist or something else that could hurt you on purpose, (b) being kicked, dragged, or beaten up on purpose, (c) being choked or burnt on purpose, and (d) being threatened or abused with a gun, knife, or other weapon. However, upon further discussion with stakeholders, our community-based partner, and pre-testing of the screening tool, we realized that these criteria would exclude most women experiencing violence and thus limit our ability to reach women in need of the intervention. As such, our screen-out criteria were adjusted to exclude women being kicked, dragged, or beaten up on purpose six or more times in the past 6 months, or those who were choked, burnt on purpose, threatened or abused with a gun, knife, or other weapon at any time in the past 6 months. Ever being hurt badly enough to require medical attention remained an exclusion criterion. All women who are screened out will receive access to referral resources for violence. In summary, the participant eligibility criteria include the following: (1) female partner between 18 and 40, (2) married, (3) speaks Kannada, (4) female partner reports male partner has a drinking problem, (5) female partner ever experienced psychological violence, and or physical, or sexual violence perpetrated by their male partner less than six times in the previous 6 months, and (6) both partners willing and able to enroll. Couples will be excluded if (1) the male partner is deemed to be severely alcohol dependent or at risk of severe alcohol withdrawal symptoms; (2) the female partner reported occurrences of severe physical or sexual violence characterized by attempting to choking or burning and threaten to use or actually used a knife or other sharp weapons against her or ever hurt badly enough that required medical attention; or (3) one or both members of the couple feared the counseling sessions may increase violence. Additional details regarding eligibility determination are described later.

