### Safety procedures and ethical approval

Studies have shown that interventions targeting women experiencing IPV can result in an escalation of violence and the participants' safety being compromised (27). Based on our past experience in recruitment of women experiencing IPV, a multi-step recruitment process has been developed, with eligibility confirmation, provision of detailed information regarding the study and informed consent occurring at a designated community center, which provides a confidential and safe space. We initially designed to contact and consent female partners first in order to offer them the opportunity to weigh the risks and benefits of participation before providing consent and allowing the research team to contact their male partner. A similar approach was successfully implemented in a study recruiting mother-in-law's of young pregnant women experiencing abuse in Bengaluru (28).

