## Conclusion

This paper reviews the study protocol for the *Beautiful Home* intervention, a three-armed randomized controlled pilot among couples in Bengaluru, India. The results of this pilot RCT will indicate whether a follow-on trial is warranted, as well as offer critical lessons for trial and intervention design. If preliminary results demonstrate that the intervention is safe and show positive improvements in male alcohol and IPV reduction, it could offer a potentially cost-efficient, scalable solution to IPV prevention in India.

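### Zero detected related harms among about 40 exposed couples is too little to call the intervention 'safe', and the safety clause makes no use of the comparison arm

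*Protocol article*

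**What the plan says.** *Expected outcomes and results* in the protocol article sets out three groups of findings that would speak for a larger trial. The first begins: "the intervention is safe and feasible (i.e., no harmful events directly related to the intervention are detected". The 'i.e.' makes this a definition. No tolerable rate, confidence limit or comparator goes with it. The second group asks for supportive outcome data, including favourable trends in drinking and IPV. The third asks that the qualitative evidence agree, including on safety. The *Conclusion* returns to the same idea: "If preliminary results demonstrate that the intervention is safe", together with improvements in drinking and IPV.

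The size of the study is given under *Sample size*: "The sample size is anticipated to be 60 couples (20 per intervention arm"). The same section says "While this sample size is not powered to detect significance" and "We anticipate attrition of approximately 20%, so our goal is to enroll 10–12 more couples to buffer these losses". *Study design* names the arms: "an incentive-only arm, an incentive-plus-counseling arm, and a comparison arm".

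Two other sections describe the harm in question. *Safety procedures and ethical approval* acknowledges that interventions for women facing IPV "can result in an escalation of violence". *Study population* sets this entry requirement for the woman: "ever experienced psychological violence, and or physical, or sexual violence perpetrated by their male partner less than six times in the previous 6 months".

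**The concern.** There are two separate weaknesses.

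- **Zero events in a small sample.** A zero count sets an upper limit on the harm rate, and with this many couples the limit is not low. The clause reports the zero as safety and leaves the limit out.
- **The relatedness filter.** Every enrolled couple has a history of partner violence, so some violence is likely in all arms. Taken alone, an episode after enrolment looks much the same whether the study provoked it or it would have happened anyway. Randomisation offers a way round this, namely an excess over the comparison arm, but the clause counts only events already judged related.

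At stake is what the pilot may say about safety when a larger trial is considered in women already exposed to violence. Escalation is a risk that the article itself names.

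**Working it through.** **1. The plan's own figure.** There is no power calculation to reproduce. The attrition allowance does reproduce: 48 / (1 − 0.20) = 60, a buffer of 12, or 50 × 1.2 = 60, a buffer of 10. Both match the stated 10–12 extra couples and a total of about 60.

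**2. Couples exposed.** Two intervention arms of 20 give 2 × 20 = 40. With 20% lost, 40 × 0.8 = 32 remain. In the combined arm the numbers are 20 and 20 × 0.8 = 16.

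**3. What zero events excludes.** The exact upper limit with zero events is 1 − α^(1/n), with α = 0.05 (one-sided 95%) or 0.025 (two-sided 95%). For n = 40: 1 − 0.05^(1/40) = 7.2% and 1 − 0.025^(1/40) = 8.8%.

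**4. Chance that the clause is met.** This is (1 − p)^n, where p is the rate per couple of harm that is both detected and judged related. The article gives no rate, so the values of p are illustrative. For n = 40: 0.98^40 = 0.45, 0.95^40 = 0.13, 0.90^40 = 0.015.

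| Couples | Upper limit, one-sided | Upper limit, two-sided | Met if p = 2% | p = 5% | p = 10% |
|---|---|---|---|---|---|
| 40 (both arms) | 7.2% | 8.8% | 0.45 | 0.13 | 0.015 |
| 32 (after 20% loss) | 8.9% | 10.9% | 0.52 | 0.19 | 0.034 |
| 20 (combined arm) | 13.9% | 16.8% | 0.67 | 0.36 | 0.12 |
| 16 (after 20% loss) | 17.1% | 20.6% | 0.72 | 0.44 | 0.19 |

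**5. Effect of the filter.** Since p counts only harm recognised as related, imperfect attribution lowers it. If the true rate were 10% and half of such events were put down to background violence (an assumption), p = 0.10 × 0.5 = 5%, and the chance of meeting the clause with 40 couples rises from 0.015 to 0.13.

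**6. What the comparison arm can add.** For 40 against 20 couples, the 95% half-width of a difference in proportions is 1.96 × √[p(1 − p)(1/40 + 1/20)]. At an assumed event rate of 10% this is 1.96 × √(0.09 × 0.075) = 16 points, and at 20% it is 1.96 × √(0.16 × 0.075) = 21 points. A two-sided 5% test would have power of about 0.14 for 10% against 20%, and 0.39 for 10% against 30%. The arm therefore supplies an estimate with a wide interval and cannot supply a useful test.

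**7. Sensitivity.** If the buffer couples come on top of 60, up to 72 are enrolled and 48 are exposed. The limits become 1 − 0.05^(1/48) = 6.1% and 1 − 0.025^(1/48) = 7.4%. The conclusion does not change.

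**The case against.** The best defence is that the clause does not stand alone. An adverse IPV trend would count against a larger trial under the second criterion, however single events were attributed, and the third brings in interview evidence on safety. Household safety is also an outcome in its own right. A reader might infer that the whole decision ignores the comparison arm, but the text does not support that. It holds for the safety clause only. The mitigation is nevertheless partial. The second criterion names no comparator and looks at aggregate trends, which can improve while a minority of couples gets worse. The third rests on interviews with about 4 couples per arm. *To assess effects on safety and intermediate outcomes* plans descriptive statistics by arm without listing IPV or harmful events. A fuller plan may do so, and I do not count that as an omission.

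Three other stronger readings also fail.

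- **One related event would end the programme.** The list gives findings in favour of a later trial and states no such rule.
- **Relatedness is judged unblinded.** The article does not say who judges it or with what knowledge of arm.
- **Forty couples can show nothing about safety.** A 10% rate of recognised harm would be missed only about 1.5% of the time.

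It is also fair to say that zero-event limits of this kind apply to any pilot of this size, that the article calls its results preliminary, and that alcohol withdrawal, another harm it anticipates, is not covered by the argument about background violence. These points reduce the weight of the concern. They do not justify defining safety as a zero count.

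**Conclusion.** The concern holds for the safety clause as written. Zero related events would exclude rates above about 7–9% across both intervention arms, about 9–11% if 20% of couples are lost, and about 14–17% in the combined arm. That is enough to make frequent recognised harm unlikely. It does not support the word 'safe' for less common serious harm: a 5% rate would meet the clause about one time in eight, and a 2% rate nearly half the time.

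The relatedness filter adds a weakness that the limits do not capture, because escalation caused by the study can pass as background violence. A reader might infer that using the comparison arm would reliably reveal such an excess. At 40 against 20 couples it would not, though it would give an estimate that does not depend on attribution.

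The figures assume independent couples, equal arms of 20 and illustrative event rates, since the article gives none.

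**What to change.** Reword the safety clause in *Expected outcomes and results* and carry the change into the *Conclusion*.

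- Tabulate all harmful events and all survey-reported increases in IPV by randomised arm, regardless of attribution and collected the same way in every arm. Define beforehand what counts as an increase.
- Give the difference from comparison with its 95% confidence interval, labelled as an estimate and not a test.
- Report related events as a secondary description, with the exact upper limit for the number of couples actually observed.
- Replace 'safe' with a bounded statement, for example: *no safety signal that precludes a larger trial was seen; related-harm rates above the calculated upper limit (about 7–9% if 0 of 40) are excluded.*

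The cost is one reworded criterion, one extra table and a more modest claim. Surveys are already planned for all arms at baseline, immediately after the intervention and 3 months later. The baseline survey covers IPV, and the criterion on IPV trends implies that the follow-up surveys do too. The intervals will be wide, with half-widths of about 16–21 points at assumed event rates of 10–20%, and should be shown as such.
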